## Abstract

**Background:**

Adequate antenatal care (ANC) and facility-based delivery are linked to improved maternal and neonatal outcomes. Adequate ANC attendance and facility birth rates are increasing in Ethiopia but remain well below national goals and global recommendations. Group ANC (G-ANC), when implemented at higher-level facilities, is associated with improved quality and experience of ANC and increased ANC retention and facility-based delivery. The objectives of this study are to evaluate the acceptability, feasibility, and effectiveness of G-ANC delivered by health extension workers at the health-post level compared to conventional ANC on ANC attendance and facility-based delivery.

**Methods:**

Group ANC will be piloted in five purposively selected health posts. The study design is a stepped-wedge trial to be conducted in 36 health posts within the catchment of six health centers, with randomization of the order of the intervention introduction done at the health-center level (clusters). The design includes three time periods: a six-month control period with no G-ANC implementation, followed by another six-month period when G-ANC will be introduced in half (n=18) of the study health posts, then a final six-month period when G-ANC will be implemented in the remaining 18 health posts. Each health post will form one cohort and conduct six monthly G-ANC meetings on a fixed day/time. The study will use quantitative and qualitative data collection approaches. The study has “pause and reflect” points designed for intervention iteration before rolling out to the next set of sites. The primary outcomes are the proportion of women with at least four ANC visits and the proportion who delivered in a health facility. Qualitative research will be conducted using in-depth interviews with pregnant women, health workers, facility managers, and regional health managers. The study will enroll 770 women across all phases.

**Conclusions:**

The study will inform decision-makers locally and globally on whether G-ANC is a feasible service delivery model at the health-post level. Effectiveness of G-ANC at increasing ANC retention and facility-based delivery and its acceptability to pregnant women and health extension workers will be reported. Registration NCT05054491, ClinicalTrials.gov (September 23, 2021).

## Introduction

Antenatal care (ANC) uptake is a key measure of progress towards improving maternal outcomes (
World Health Organization, 2016a). Although improvements have been made in the uptake of at least one ANC contact in Ethiopia, attendance for the recommended number of contacts remains low. The 2016 Ethiopia Demographic and Health Survey (EDHS) reported that 62% of pregnant women aged 15–49 received any ANC from a skilled provider, 32% had at least four ANC contacts, and 26% gave birth in a facility (
CSA/Ethiopia & ICF, 2017).

In Ethiopia, women are expected to receive ANC from health centers (HCs) and health posts (HPs) (
Assefa *et al.*, 2019). HCs provide comprehensive maternal health services, and HPs deliver primary health care packages, including ANC (
Gebretsadik *et al.*, 2019). Each HC typically has up to five affiliated HPs in its catchment area. HPs are staffed by health extension workers (HEWs) who are salaried female community health workers recruited from the community (
Kea *et al.*, 2018;
Tsegay *et al.*, 2013). HEWs complete a one-year basic health service delivery course, and about 50% have received an additional year of training (
Ministry of Health Ethiopia, 2022). HEWs are expected to spend 75% of their time in communities. At least two HEWs are assigned to one HP to serve a population of 3,000 to 5,000 in a village (
*kebele*). Since 2020, the Ministry of Health (MOH) has taken steps to move more ANC services, including diagnostics, to the HP level (
FMoH, 2020). Each HP (where HEWs work) is generally supported by health workers from the nearby HC, who provide supervision, technical support, and clinical services that are beyond the scope of HEWs. Typically, HEWs refer cases that need more advanced care to HCs. The MOH supports several community-based interventions to increase awareness about danger signs and the importance of skilled care at birth, including mobilization of unpaid female volunteers (i.e., women’s development army leaders). Also, HEWs coordinate meetings for pregnant women conferences that are conducted monthly at the village level by a nurse/midwife (
Asresie & Dagnew, 2019).

The World Health Organization recommends G-ANC in the context of rigorous research as an alternative to individual ANC (
World Health Organization, 2016b). G-ANC is a transformative service delivery model that provides care to groups of eight to 10 pregnant women of similar gestational age through a series of scheduled meetings (ANC) (
Sharma *et al.*, 2018). Several studies have found that G-ANC is associated with increased ANC attendance, improved health literacy and client satisfaction, increased uptake of family planning, improved birthweight, and increased breastfeeding initiation/duration (
Hale *et al.*, 2014;
Manant & Dodgson, 2011;
McKinnon *et al.*, 2020).

This study will evaluate the acceptability, feasibility, and effectiveness of G-ANC delivered by HEWs at the HP level compared to conventional ANC among women who report intention to receive ANC at the HP level. It builds on existing local efforts and addresses important questions regarding how ANC service delivery might be modified to improve quality (both provision and experience) of care. This proposed study will introduce G-ANC at a lower level of the health system (i.e., the HP) to address a key element of the global G-ANC learning agenda: can the model feasibly be delivered by community-based providers closer to women’s own homes and communities, while retaining quality of care and other positive outcomes associated with G-ANC at higher-level facilities (
Grenier *et al.*, 2020). The proposed G-ANC intervention at the HP level will be led by HEWs. G-ANC will build from group education activities at HPs and support service delivery reorganization into G-ANC to test potential improvements in ANC attendance and facility-based delivery, both of which are MOH priorities.

## Methods

### Study design

This mixed-methods study will use a stepped-wedge cluster randomized controlled trial with randomization of the order of the start of the intervention done at the HC level (clusters) in the Amhara region of Ethiopia. The study will begin with a pilot to test the feasibility of the intervention conducted by HEWs at the HP level. If feasible, a randomized controlled trial will be conducted with three time periods: baseline period (T1), time period 2 (T2), and time period 3 (T3), each about six months in duration. The control period for the first half of clusters will occur at T1. These clusters will start G-ANC first at T2. These clusters will have a choice to continue G-ANC with a second cohort of women during T3 (
Figure 1). The control period for the second half of the clusters will occur at T2. The second half of the clusters will start the intervention in T3. We plan to use a stepped-wedge study design because it allows for iterative learning (i.e., adaptive management) during the study to modify the intervention, which was novel compared to traditional cluster randomized control trials. The study was registered on September 23, 2021, on clinicaltrials.gov with registration ID: NCT05054491.

**Figure 1. f1:**
[figure not shown]
Time steps and clusters for G-ANC at the HP level.

Prior to the intervention, all women in the study HPs will receive the current standard of individual ANC. HPs primarily offer ANC and other preventive services but do not provide delivery care. At the time of the intervention, the HP in the selected clusters will provide G-ANC to one cohort of eight to 10 pregnant women. Group ANC participants will be followed prospectively from the time of study enrollment. All non-enrolled pregnant women in the intervention HP will continue to receive individual ANC. During the control period, care is provided in the same setting (HP) by the same personnel (HEW). The main difference is that the control group receives individual care, while the intervention group receives care in a group-based care model.

### Study setting

The G-ANC study will be conducted in two zones of the Amhara regional state: West Gojjam Zone (South and North Achefer districts) and the South Gondar Zone (Farata, Dera, and Libokemem districts). Twelve HCs in the Amhara region will be selected as G-ANC study centers. G-ANC meetings will take place at the HP level only. Amhara region has an estimated population of 22.5 million (
CSA/Ethiopia & ICF, 2017) and 12 administrative zones. The economy is primarily subsistence farming.

### Participants

Twelve HCs will be selected in the Amhara region after meeting the eligibility criteria (
Table 1) and categorized by 1) type of location (peri-urban or rural) and 2) client volume for the last year (low or high). Each of the six HCs will have three HPs, and these will be randomized in a sequence of receiving the intervention. Study participants will be pregnant women attending ANC, HEWs, and facility and regional managers working in study sites in Amhara region.

**Table 1. T1:** Facilities and study participants inclusion and exclusion criteria.

Facilities and study participants’ inclusion and exclusion criteria		
Health facilities	Inclusion criteria	For HCs: • Located in Amhara, Ethiopia • Have HPs in the catchment area that provide point-of-care testing • Affiliated with functioning HPs where HEWs provide ANC • Permission granted by health facility management to participate in the study For HPs: • A minimum of two HEWs per HP (one of whom is a level-four HEW with an additional year of training) • On-site availability of ANC services, including on-site point-of-care tests • Have adequate space to hold G-ANC meetings • Permission granted by HP management to participate in the study • Enroll a minimum of 10 new ANC clients per month who are ≤ 20 weeks gestational age, as determined by the health management information system (subject to change based on the results of the pilot phase)
**HEWs**	Inclusion criteria	• Working in a participating/selected health facility and providing ANC services • Willing to participate in the study • Based in the selected HP • Agree to provide G-ANC
**Health facility managers & regional health managers**	Inclusion criteria	• Working in Amhara region for at least six months before the start of the study
**Pregnant women (ANC clients)**	Inclusion criteria	• Minimum age of 15 years at the time of enrollment; pregnant 15–17-year-olds will be treated as emancipated/mature as per local regulations • Gestational age ≤ 20 weeks at the time of enrollment determined by last menstrual period, pelvic exam, fundal height, quickening, ultrasound, and/or timing of fetal heart tones and pregnancy test* • Able and willing to provide adequate locator information • Planning to reside at their current location for at least 10 months • Agree to participate in the study and continue ANC at HP • Willing to participate and consent to follow-up for up to six weeks post-delivery • Willing to receive G-ANC at the HP level (during the intervention period)
	Exclusion criteria	• Plan to travel away from the study site for more than four consecutive weeks during ANC or before six weeks post-delivery • Unable to provide consent • Have any condition that, in the opinion of the investigator or designee, would complicate interpretation of study outcome data or otherwise interfere with achieving the study objectives

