### Intervention

During the intervention time period, pregnant women who come for their first ANC visit at the HP will receive standard individual care. At the end of this first ANC visit, eligible women who agree to participate in G-ANC will be added to the G-ANC cohort. Approximately eight to 10 women will be enrolled in a cohort. Cohort membership will be fixed (i.e., the same women and facilitators at each meeting). Two additional pregnant women who meet study criteria can be added to a G-ANC cohort if added to the cohort by the start of the second G-ANC meeting. Six monthly G-ANC meetings will be conducted for each cohort on a fixed day/time at each HP. Each cohort will meet for G-ANC meetings in a designated meeting space that is set up to ensure privacy during clinical consultations. The G-ANC meeting will be conducted by at least one HEW who is trained in the G-ANC service delivery model.

Each meeting will have the same general structure: self-assessment by the clients/peer-to-peer self-assessment initially taught and supervised by the HEW, such as measurement of weight and blood pressure using an automated cuff; individual assessments/clinical care by the HEW in a private space; discussions around pre-determined and appropriate gestational-age themes using illustrative cards and take-home booklets designed for G-ANC; and plan/reflect and peer-support activities that create group cohesion.
Table 2 presents the G-ANC meeting schedule and content per meeting. Each meeting is expected to last 90–120 minutes and will be documented as an ANC contact. Social distancing in response to COVID-19 as per national guidelines will be enforced during meetings. Women will have the opportunity for additional private time with the HEW after the G-ANC meeting if desired or needed for health and/or safety. Women will be told that they can and should return at any time if they have questions or concerns. Phone/text reminders will be used to remind participants of G-ANC meetings as a strategy to improve ANC attendance.

**Table 2. T2:** G-ANC intervention meeting schedule.

Meetings	Timing (gestational age)	Theme/Meeting Plan
Meeting 1	4–5 months	• Introduction to group care • Preventing problems in pregnancy • Teach self-assessments
Meeting 2	5–6 months	Danger signs during pregnancy • Sexually transmitted infection (STI) transmission and partner communication/negotiation

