### Recruitment and consent

ANC clients will be recruited via four strategies: 1) pregnant women will be identified in the community as potential study participants through existing local community structures (such as the women’s development army leaders) so that the study can be explained to potential participants and they can be linked them to an HEW for their first individual ANC contact and to a data collector; 2) all new ANC attendees in the intervention HPs will be screened for eligibility during the first ANC contact with an ANC service provider; 3) women who come to the HC for their first ANC visit will receive their first individual ANC visit at the HC and then be linked to a catchment HP for eligibility assessment and enrollment if they consent to participate; and 4) eligible women will be identified by G-ANC-trained HEWs who make door-to-door visits in the community.

Research assistants will rotate among each of the intervention HPs during the recruitment period to explain the study to women who meet the inclusion criteria and agree to participate in the study.

The research assistants will obtain verbal consent from women in a private space in the HP using institutional review board (IRB)-approved recruitment and consent documents in the local language. Verbal consent will be sought instead of written consent as written consent is seen as a personal identifier in the community and verbal consent is preferred. This consenting method was approved by the ethics committee (see Ethics section). The potential G-ANC participants will be informed during the consenting process of the expected number of meetings (i.e., ANC visits) and their rights, risks, and benefits. The research assistant will explain the need to collect their names, phone numbers, and addresses, which will be used for study-related follow-up purposes only. Anyone declining participation in the study will be referred to individual ANC care during the intervention period. A baseline questionnaire will be administered to consenting study participants at the beginning of each step (time period).

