For HEWs and health facility managers, study staff will explain the purpose based on the inclusion criteria. The HEWs will be oriented to the study including the randomization (they will not be blinded to the order of randomization of their HC and affiliated HPs) and their role in the study including screening first-time ANC clients for eligibility to participate. HEWs who will be facilitating G-ANC meetings will be informed that they may be asked to participate in an in-depth interview (IDI) at the end of the study related to implementation of group-based care and its effect on their job and satisfaction levels. Oral consent will be obtained in a private location at the health facility by research assistants.

For the regional health managers, study staff will contact the regional health bureau responsible for overseeing reproductive health programs in the Amhara region via phone or in-person and invite the regional health manager to participate in an IDI as per the inclusion criteria. An appointment will be scheduled to obtain informed consent and conduct the IDI, preferably at the regional health bureau office. Written consent will be obtained by the research assistant who will conduct the interview in a private location.

For the IDIs of women and HEWs involved in G-ANC, qualitative data will be collected at the end of the study after all G-ANC meetings have been conducted. Oral consent will be obtained from the HEWs and eligible women three to six months postpartum to be enrolled in the qualitative portion of the study.

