### Data collection

Both quantitative and qualitative data collection approaches will be used in this study. Data will be collected in the pilot phase and then during study implementation (Phase 2).

Once enrollment begins, all new ANC attendees in the selected HPs will be screened for eligibility during the first ANC contact with a health care provider. The screening and enrollment questionnaire will be completed. Basic demographic data will be collected from all eligible consented women (all who meet the inclusion criteria). All data will be de-identified for those who decline study participation. Baseline and endline data will be collected from all eligible and voluntary women participating in all study time periods. During the first period, data will be collected from 18 control HPs. In the second period (T2), data will be collected from 18 intervention and 18 control HPs. In the third period, (T3) data will be collected from 18 intervention HPs.

Data quality will be monitored through the use of trained research assistants and supervisors, data quality supervision, and use of an electronic data collection program to minimize data entry errors.

The study team will select respondents for the IDIs at the end of the study based on preliminary findings from the quantitative survey. IDIs with women will be conducted at the end of T2 and T3, after completion of all G-ANC meetings (
Table 7). Specific topics/domains to explore with G-ANC participants include satisfaction with care, any perceived changes in self-efficacy or empowerment, health literacy, improved communication and/or trust with providers and the health system as a whole, factors in uptake/non-uptake of postpartum family planning, and the overall impression of the G-ANC model. In this study, we will use standardized pretested tools to assess the levels of empowerment, self-efficacy, and satisfaction. For empowerment and self-efficacy, we will use eight questions related to their current pregnancy and calculate a composite score to understand the woman's level of empowerment. We will ask 11 questions about their satisfaction with the ANC received during their last pregnancy and with the G-ANC for their current pregnancy.

**Table 7. T7:** Data collection timing, per tool.

Data collection tool	Study participant	Timing of data collection		
		T1	T2	T3*
Cluster level information	HP level information	18 HPs	36 HPs	18 HPs

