### Data analysis

**
*Quantitative data analysis.*
** Data analysis and the reporting of results for this study will be conducted in accordance with norms for analyzing cluster randomized trials as described in the Consolidated Standards of Reporting Trials guidelines with considerations for the step-wedge extension (
Hemming *et al.*, 2018;
Hemming *et al.*, 2019). If there is variation within the clusters, the statistical analysis will be adjusted based on the pollution levels. The primary analysis will be conducted using intention-to-treat analysis. After exploring balance by time period/intervention status and correlations, the effect of G-ANC will be estimated using generalized linear mixed effects models with binomial distribution and logit-link. The model will include G-ANC as the intervention indicator, time period and their interaction as the primary predictors, and HC as the random intercept. We will adjust for facility- and individual-level characteristics that show imbalance between the intervention vs. control time periods and can be strongly correlated with the outcome scores. The primary outcomes will be compared across time periods both within the intervention and control groups. Comparisons will be made within a given time period (e.g., T1, T2, and T3) for both the intervention and control conditions. The amount of missing data will be assessed for each variable and overall, for the sample. If more than 5% of data on covariates are missing, multiple imputation procedures will be used assuming data are missing at random (
Sterne *et al.*, 2009).

**
*Qualitative data analysis*.** Following each audio recording, either the moderator or an official transcriber familiar with local language and English will transcribe from the audio recording. Analysis will be thematic content analysis with similar themes and subthemes. Coding of textual passages will be done using open code 4.03 Umeå: Umeå University, an open-source tool known for qualitative analysis.

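### Willingness to receive G-ANC is an entry criterion only in the intervention period, so the two conditions enrol through different filters and the intention-to-treat label does not repair this

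*Protocol article*

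**What the plan says.** Table 1 (Participants) gives the entry criteria for women. Most apply in every period, including "Agree to participate in the study and continue ANC at HP", along with criteria on residence, locator details and follow-up. One applies in only one condition: "Willing to receive G-ANC at the HP level (during the intervention period".

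The Intervention section says that, after a first individual visit, "eligible women who agree to participate in G-ANC will be added to the G-ANC cohort". Under Study design, "All non-enrolled pregnant women in the intervention HP will continue to receive individual ANC". Recruitment and consent adds: "Anyone declining participation in the study will be referred to individual ANC care during the intervention period". On outcome data, Data collection says: "Baseline and endline data will be collected from all eligible and voluntary women participating in all study time periods". It mentions de-identified data for women who decline the study, but no endline survey for them.

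Allocation comes first. Randomization places the 1:1 allocation of health centers before T1, and women are recruited afterwards. Health extension workers screen first-time clients, and "they will not be blinded to the order of randomization of their HC and affiliated HPs". Field workers of the research institute take consent and enrol, and study staff are not blinded either.

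Data analysis states: "The primary analysis will be conducted using intention-to-treat analysis". It also provides for adjustment for facility and individual characteristics that turn out imbalanced.

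**The concern.** Cluster randomisation protects the comparison only if women enter each condition in the same way. Here a woman in an intervention period enters the data set only if she accepts a programme of six monthly group meetings. A woman in a control period is never asked.

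The filter is also close to what is measured. Women are told the expected number of meetings during consent, each meeting is recorded as an ANC contact, and the first primary outcome is four or more contacts. Women who foresee that they cannot come monthly are likely to decline, and they then drop out of one condition only.

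An intention-to-treat analysis keeps enrolled women in their condition. It cannot bring back women who were never enrolled because they declined. Adjusting for measured characteristics does not capture motivation. At stake is whether an observed odds ratio reflects group care or the kind of woman who agrees to it.

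**Working it through.** **Inputs from the protocol (Sample size, Table 4).** Control proportions are 0.315 (four or more ANC contacts) and 0.271 (facility delivery). The target odds ratio is 2, with 12 health centers, 30 women per cluster-period, ICC 0.100 and a 0.05 level (two-sided assumed here).

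**The plan's own figures.** For ANC, 2 × 0.315/0.685 = 0.920, and 0.920/1.920 = 0.479 (stated 0.48). For delivery, 2 × 0.271/0.729 = 0.743, and 0.743/1.743 = 0.426 (stated 0.43). A standard stepped-wedge variance (fixed period effects, random cluster intercept, variance at the control proportion) gives 83.9% and 83.1% power for the complete design, against 84% stated. Other variance conventions give 73% to 81%. The issue here is bias, not the power arithmetic.

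**Assumed, because the documents are silent:** the share d of otherwise eligible women who decline G-ANC, and the outcome rate q they would have had. The true effect of G-ANC is set to zero.

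If control women are a mix of would-be joiners and would-be decliners:

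- joiner rate = (0.315 − d·q)/(1 − d)
- excess over control = d(0.315 − q)/(1 − d)
- spurious OR = odds(joiner rate)/odds(0.315), with odds(0.315) = 0.460

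The excess is positive if q is below 31.5%, zero if equal and negative if above. The sign therefore depends on q.

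| d | q | joiner rate | excess | spurious OR | share of log 2 |
|---|---|---|---|---|---|
| 10% | 20% | (0.315 − 0.020)/0.9 = 0.328 | 1.3 points | 0.488/0.460 = 1.06 | 8% |
| 20% | 20% | (0.315 − 0.040)/0.8 = 0.344 | 2.9 points | 0.524/0.460 = 1.14 | 19% |
| 30% | 15% | (0.315 − 0.045)/0.7 = 0.386 | 7.1 points | 0.628/0.460 = 1.37 | 45% |

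The last row is at the strong end: it implies a joiner-versus-decliner OR of 0.628/0.176 = 3.6.

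**Wider range.** Spurious OR for a joiner-versus-decliner OR of 1.5 / 2 / 3, again with zero true effect:

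| Accepting G-ANC | Four or more ANC (31.5%) | Facility delivery (27.1%) |
|---|---|---|
| 90% | 1.04 / 1.06 / 1.09 | 1.04 / 1.06 / 1.09 |
| 70% | 1.12 / 1.21 / 1.32 | 1.12 / 1.20 / 1.31 |
| 50% | 1.22 / 1.38 / 1.64 | 1.21 / 1.38 / 1.62 |

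This is about 5% to 71% of the log odds ratio the trial is sized for.

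**False-positive probability.** Put z = excess/SE and compute Φ(z − 1.96) + Φ(−z − 1.96). For the complete design the result runs from 5.2% to 51% over this grid. In the largest case the excess is 0.114 and the SE about 0.058. With data in only two periods per health center, as Data collection describes, the SE is about 0.101 in that case and the range is 5.1% to 21%.

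**What including decliners would do to a true effect.** Suppose joiners have a true OR of 2 and decliners no effect.

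- d = 20%, q = 20%: joiner odds 2 × 0.524 = 1.048, rate 0.512. All-comer rate 0.8 × 0.512 + 0.2 × 0.20 = 0.449, and OR = 0.816/0.460 = 1.77.
- d = 30%, q = 15%: joiner odds 2 × 0.628 = 1.256, rate 0.557. All-comer rate 0.7 × 0.557 + 0.3 × 0.15 = 0.435, and OR = 0.769/0.460 = 1.67.

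These lose about 17% and 26% of the log odds ratio.

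**The case against.** The best defence is that both conditions are already selected for commitment to ANC. Every woman agrees to continue ANC at the health post, plans to stay for at least 10 months, accepts follow-up to six weeks after delivery and enters by 20 weeks. All new attendees are to be screened, and field workers of the research institute, not the health extension workers, take consent. That stands, and it limits the extra selection to what the group offer adds. It does not remove the difference between conditions.

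The documents do not support four stronger readings that a reader might infer:

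- **That the controls are unselected.** They are not. Only the G-ANC filter differs.
- **That the odds ratio is certainly inflated.** This needs decliners to do worse than joiners, which no section states. Some women may decline because they prefer individual or health-center care, and their attendance or facility delivery could be as good or better. The 31.5% is also a regional figure, not a rate among women who passed the entry criteria.
- **That the screening log gives the decline share.** Table 7 names the log but does not show that it records refusal of G-ANC or the reason. The sentence on referring decliners concerns declining the study, and basic demographics are planned for women who meet all criteria. T2 data on refusals may be incomplete.
- **That dropping the criterion in T3 yields an unbiased, barely diluted estimate.** T2 and T3 intervention samples would then come from different populations, in different sequences and periods. Unblinded identification of women would remain, and the dilution shown above is not negligible.

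**Conclusion.** The concern holds in this form: one condition has an extra, post-allocation entry filter close to a primary outcome, and the women it removes have no outcome data. Neither the intention-to-treat statement nor adjustment for measured imbalance corrects that.

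Upward bias is the plausible direction for four or more visits, conditional on decliners attending less. For facility delivery the direction is less clear, though similar assumptions give similar sizes. The size cannot be fixed from the documents. It is small at about 90% acceptance and material at 50% to 70% if joiners and decliners differ clearly. Until refusals are known, a positive result cannot be attributed to G-ANC without this qualification.

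**What to change.** 1. Report, by condition and period, the number of otherwise eligible women not enrolled because they declined G-ANC. For T2, use the screening records as far as refusals were logged. In T3, log refusal and reason prospectively.
2. Pre-specify, for both primary outcomes, a sensitivity analysis that returns decliners to the intervention condition over a range of assumed outcome rates. State the decline share and rate at which the conclusion changes.
3. Describe the primary analysis as one of enrolled women by allocated condition, where enrolment in the intervention periods required acceptance of G-ANC. Do not call it intention-to-treat without that qualification.
4. Optionally, in T3, enrol on the common criteria before the G-ANC offer and follow consenting decliners with the existing baseline and endline tools. Use the result to inform the sensitivity analysis. Acknowledge the difference between T2 and T3 samples, the dilution and the remaining unblinded identification.

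Study status reports the T1 and T2 surveys as done and T3 as in preparation, so the T3 steps are still open. Items 1 to 3 cost a little logging and analysis, and a less favourable label for the main result. Item 4 costs more: each health post forms one cohort of about eight to 10 women, so following decliners means more women per post or smaller groups.
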